## A.6 PROCEDURES

A.6.1 What procedures or methods will be employed in the collection of data (e.g. patient interviews / focus group discussions / blood sampling / biopsies) and by whom (e.g. experienced facilitator / social scientist / teacher/ qualified doctor / nurse, auxiliary, etc.)?

Attach additional sheets if necessary.

| Method                                | To be carried out by:                                   |
|---------------------------------------|---------------------------------------------------------|
| Patient interviews                    | Midwife Research assistants (4)                         |
| Blood samples                         | Midwife Research Assistant or Laboratory Technician (2) |
| Observations                          | Midwife Research assistants                             |
| Preparation of treatments to be given | Pharmacy technician (2)                                 |
| Data entry                            | Qualified data clerks (2)                               |

A.6.2 State the extent to which the procedures to be used are a part of usual clinical management (if appropriate).

- Observations proposed are routinely done to monitor progress of labor
- Blood samples are sometimes requested for Hb, grouping and cross matching in case there is an indication for possible PPH

A.6.3 Please indicate that the persons identified in A.6.1 are competent to carry out these procedures. List any training of staff that may be required prior to commencement of the study.

The project personnel will include qualified midwives to collect blood samples and data (both interviews and observations), a laboratory technician to collect blood samples, a pharmacy technician to prepare the proposed treatments and a data clerk to double check and enter data

## A.7 ANALYSIS

[PPH RCT Study protocol-version 2.0 June 18th 2012]

[figure not shown]

A.7.1 What are the major statistical (or other) methods that you intend to use to analyse the data to fulfil each of the objectives/hypothesis stated in A.3

### Data Preparation

All data will be cross checked for completeness before discharge of mothers. Data will be coded and entered independently into access database and exported into STATA version 12.0 (Statacorp, College Station, Texas, USA) for statistical analysis.

### 3.4.3 Data Reporting

Results will be analyzed and presented as per the current CONSORT guidelines (Piaggio et al, 2006). The proportions will be presented as percentages and their confidence Intervals will be presented at 95% (two-tailed) at the power of 95%. Two-tailed statistical analysis will be used and statistical significance will be defined at level of  $p \leq 0.05$ . If the lower limit of the 95% confidence interval lies to the right of the non-inferiority margin ( $\Delta$ ) the experimental intervention will be regarded "**inferior**". If results lie left of  $\Delta$ , it will be concluded as **non-inferior** with regard to that pre-stated margin  $\Delta$ . If the results are inconclusive regarding the non-inferiority hypothesis and the whole 95% confidence interval lies to the right of zero, it will be concluded that the misoprostol is **significantly worse** according to a superiority hypothesis.

[figure not shown]

## A.8 QUALITY ASSURANCE

A.8.1 What procedures are in place to ensure the quality of the data?

*Guidance notes:*

*For qualitative data (for example) what procedures will be used to check translations or compare data obtained from different sources?*

*For quantitative data (for example) how will transcription errors be minimised?*

*Give some detail on how methods are going to be piloted, if appropriate*

- An instrument to collect the required data has been adapted from the tools used by other researchers in other sites.
- Computer-generated numbers will be used to randomize mothers into this study. These numbers will be in opaque envelopes to blind the observers on the group to which the next mother will be randomized and observed. The Investigator or midwife researchers/ observers will not have prior knowledge of the treatment allocated to the next patient to avoid bias into the random allocation process.
- Double blinding will be done by administration of 1 ml of normal saline or water for injection to the misoprostol group to mimic oxytocin injection. **All the inactive agents (dummy oxytocin/ water for injection and placebo for misoprostol) will be packaged to exactly resemble the actual drugs themselves to ensure effective double blinding.** The comparison group on the other hand involving the standard/ gold oxytocin as a prophylactic uterotonic agent will also receive a placebo taken sublingually to blind for misoprostol.
- Details of the aim and procedures to be involved in the trial for both oxytocin and misoprostol groups, potential side effects and therapeutic benefits will be explained to the eligible patients on admission by the midwife researcher before consent and randomization occurs. Once the mothers consent to participate in the study, they will be monitored for labor and opaque envelopes containing computer-generated consecutive numbers from 001-1140 will then be opened once vaginal delivery is deemed inevitable.

[figure not shown]

- Improved routines at the labor ward will be targeted and all mothers on the ward regardless of the intervention will be treated similarly. A 'PPH Trolley' will be freely provided at all times in the labor ward to improve availability and accessibility of these uterotonics.
- All blood samples for complete blood count will be labeled properly using patient random study numbers on the laboratory request form, interview guides and observation forms. Laboratory tests and examinations will be done by two specific laboratory technicians to ensure consistency. All samples will be stored in the same laboratory to ensure consistency and accuracy. Blood samples will be randomly selected and tested in another laboratory for quality checks, consistency and accuracy.
- Sublingual route of administration of misoprostol will be preferred due to its pharmacodynamics properties including rapid onset of action, greater bioavailability and prolonged activity (Hofmeyr, 2005; Khan, 2003; Abdel-Aleem, 2003). Similar misoprostol doses will also be maintained and administered once to avoid variations in plasma therapeutic levels (Mousa and Alfirevic, 2009)
- After the baby has been born, the amniotic fluid will be drained immediately and a plastic sheet will be placed under the mother's buttocks to collect blood during and after third stage of labor. After the delivery of the placenta, mothers will be asked to put on similar pre-weighed sized pads for the next 24 hours.
- Electronic weighing scales will be standardized and some bloody mops will be sampled and weighed using other alternative scales from time to time to ensure consistency and accuracy
- An internationally recognized brand of misoprostol (cytotec) or its equivalent from a company with International Good Manufacturing Practice will be used for this study
- Four midwives will be **recruited** and **trained** as observers to increase accuracy and consistency in estimation and recording of blood loss plus other treatment outcomes. They will be assisted by the labor staff and these outcome assessors will be blinded to the interventions and hypotheses of this study. To minimize observer bias and facilitate patient and observer randomization, each

[figure not shown]

research assistant will be assigned the even or odd study numbers alternating every time an eligible mother is identified. Senior Obstetricians will supervise the trial, collection and recording of blood and other treatment outcomes on maternity ward. Observations will be done from the onset of 3rd stage of labor to 24 hours after delivery.

- Expired blood will be obtained and used in training on estimating spillage on floor, tables and garments in case it occurs. These spills on garments, floor and tables will be minimized. The bloody pads for the next 24 hours will be measured soon after delivery to avoid drying and evaporation.
- **A safety monitoring committee incorporating the independent members with expertise in Obstetrics and Statistics will be constituted to ensure safety of participating mothers.** Four safety checks will be done at 25% recruitment, 50%, 75% and at the end of data collection.
- All laboratory tests will be independently done by qualified staff in Mbarara University of Science and Technology Research laboratory. Similar calibrated containers and 1g pre-weighed cotton pads will be utilized to collect and estimate blood loss. **A spare laboratory technician will be hired and on hand to back up or handle laboratory tests at all times**

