## **SECTION C RESPONSIBILITY**

### **C.1 Litigation:**

In respect of any litigation which may result from this research

a) Who will provide compensation?

Misoprostol 600ug and lower doses have been documented to be safe when used for PPH prevention and or treatment. Particular litigation is not envisaged in the overall AMASA research framework or this particular study. However, this issue will be brought to the attention and review of the Data and safety Monitoring committee in case safety issues do arise.

This data and safety monitoring committee will constitute the senior staff on the maternity ward to ensure safety of participating mothers. Four safety checks will be done at 25% recruitment, 50%, 75% and at the end of data collection.

(Please provide documentary evidence where appropriate.)

b) What insurance arrangements have been made by the applicant and his/her delegated assistants?

As in C.1 a. above

(Please ensure that any professional indemnity insurance is logged with the Director's office)

[figure not shown]

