## Data Safety and Monitoring Board and stopping rules

1. Assoc. [name], PhD (Mbarara University of Science and Technology
2. [name] [name], Mmed Obs/ Gyn, Senior consultant, Mbarara Regional referral hospital
3. [name], Mmed Obs/Gyn, Mbarara University of Science and Technology
4. [name] (Bio-statistician), Medical Research Council, Entebbe
5. [name], PhD, Deputy Principal, Makerere University College of Health Sciences

This is purely an independent DSMB from Mbarara University, Makerere University, Mbarara Hospital and an independent biostatistician working with a reputable research organization in Entebbe. The preliminary results will be reviewed at 50% (570), 75% (855) and completion. The committee will base their decision to stop the trial after consideration of disadvantages of the treatment arm over the conventional/control arm and its likelihood to affect not only maternal clinical outcomes but also practice for both acute and severe PPH. This decision will be based on a two-sided superiority hypothesis.

[figure not shown]

Supplement: Text S1 — Trial protocol. (PDF) [file pmed.1001752.s003.pdf]

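### The protocol describes the safety committee both as senior ward staff and as a purely independent board, and does not fix whether that board meets, with power to stop, at 25% recruitment (285 mothers)

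*Protocol*

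**What the plan says.** **Timing.** Section A.8 (Quality Assurance) and section C.1 (Litigation) carry the same sentence: "Four safety checks will be done at 25% recruitment, 50%, 75% and at the end of data collection". The section on the Data Safety and Monitoring Board and stopping rules gives a different list: "The preliminary results will be reviewed at 50% (570), 75% (855) and completion". That section alone says how a stop would be decided: "The committee will base their decision to stop the trial after consideration of disadvantages of the treatment arm over the conventional/control arm", on a two-sided superiority hypothesis.

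**Membership.** The protocol gives three descriptions:
- A.8: "A safety monitoring committee incorporating the independent members with expertise in Obstetrics and Statistics".
- C.1: "This data and safety monitoring committee will constitute the senior staff on the maternity ward to ensure safety of participating mothers".
- Stopping-rules section: a list of five members, introduced with "This is purely an independent DSMB from Mbarara University" and continuing with Makerere University, Mbarara Hospital and an outside biostatistician. One listed member is described as "Senior consultant, Mbarara Regional referral hospital".

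**Outside the schedule.** C.1 says of possible litigation that "this issue will be brought to the attention and review of the Data and safety Monitoring committee in case safety issues do arise". A.8 also has senior obstetricians supervising the trial and the recording of outcomes on the same ward.

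**The concern.** Two things that a monitoring plan has to fix are described in more than one way.

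The first is who monitors. Read literally, C.1 hands the checks and the ad hoc referrals to senior staff of the ward where the trial runs. The stopping-rules section hands the reviews to a listed board that it calls independent. Both cannot describe the same committee, and following one breaches the other.

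The second is when the body that can stop the trial first meets. A team that works only from the stopping-rules section would hold its first scheduled review at 570 mothers, half the trial. Before that, only the ad hoc referral in C.1 would remain, and its recipient is the committee whose membership is in doubt.

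Misoprostol replaces the standard uterotonic in a trial whose primary outcome is blood loss of 500 mL or more. What is at stake is mothers' safety and the independence of oversight.

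**Working it through.** **1. The plan's own counts.** The total is 1140 (A.4). 0.50 × 1140 = 570 and 0.75 × 1140 = 855, as printed in the stopping-rules section. By the same rule 25% is 0.25 × 1140 = 285, which the protocol does not print.

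**2. The texts side by side.**

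| Section | Scheduled looks | Committee | Basis for stopping |
|---|---|---|---|
| A.8 | 25%, 50%, 75%, end | incorporates independent members | none stated |
| C.1 | 25%, 50%, 75%, end | senior ward staff | none stated |
| Stopping rules | 50%, 75%, completion | listed, purely independent | disadvantage of the treatment arm |

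The membership conflict lies between C.1 and the stopping-rules section. A.8 does not exclude ward staff, so it does not itself contradict C.1. On timing, only the 285 look differs.

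**3. Calendar time.** B.3.1 gives a maximum of about 2 years. If accrual is even (an assumption), 1140 / 24 = 47.5 mothers a month, so 285 is reached at 6 months and 570 at 12.

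**4. What a stop at 285 could achieve.** The rates come from A.5.4: 14% with oxytocin, 20% with misoprostol, 28% with no uterotonic. Assumptions: 142 mothers per arm, a pooled z-test, and two-sided levels of 0.05, 0.01 and 0.001, since the protocol states no interim level. The probability that misoprostol is shown worse is by exact binomial enumeration. Between 285 and 570, 285 / 2 = 142.5 mothers would receive misoprostol. So the expected cases avoided, if the stop is immediate, are probability × 142.5 × risk difference. The multiplier is 142.5 × 0.06 = 8.55 or 142.5 × 0.14 = 19.95.

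| Misoprostol v oxytocin | Probability at 0.05 / 0.01 / 0.001 | Cases avoided |
|---|---|---|
| 20% v 14% | 0.271 / 0.110 / 0.023 | 2.31 / 0.94 / 0.20 |
| 28% v 14% (no effect, worst case) | 0.834 / 0.637 / 0.343 | 16.65 / 12.71 / 6.84 |

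**5. What it costs when the arms are equal (14% each).** The 285 look alone stops wrongly for harm with probability 0.0252 / 0.0050 / 0.0004 (exact). The table gives simulated results with the same level at each look. Non-inferiority means 570 per arm, an upper 95% limit below 6%, and no stop.

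| Two-sided level | False stop, looks at 570 and 855 | False stop, 285 added | Chance of non-inferiority, without v with 285 |
|---|---|---|---|
| 0.05 | 0.0385 | 0.0540 | 0.8264 v 0.8174 |
| 0.01 | 0.0082 | 0.0123 | 0.8313 v 0.8298 |
| 0.001 | 0.0008 | 0.0012 | 0.8320 v 0.8319 |

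A second simulation gave 0.0009 and 0.0013 in the last row, which is within simulation error. The exact 0.0004 caps the true rise at that level, and caps the loss in the chance of non-inferiority at 0.04 percentage points.

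**The case against.** The best defence on timing is that safety checks and reviews of preliminary results are two different activities. A safety check at 25%, followed by comparative reviews at 50%, 75% and completion, is a coherent plan. The 25% check is promised twice and withdrawn nowhere, and the sentence on stopping is not tied to any one look. This largely stands. A reader might infer that the 25% check has been dropped, or that nobody may stop the trial before 570. The documents support neither. But the protocol never says that the two activities are separate, and three of the four time points coincide. Even on this reading it remains open whether the listed board meets at 285 with power to stop.

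On membership, the defence is that one loose sentence in an answer about litigation should yield to a dedicated section with a list of members. That is probably how the trial team would read it, and the hospital consultant on the list may explain the wording. It is still a direct contradiction about who protects participants. A reader might also infer that the people running the trial would be monitoring it, because senior obstetricians supervise outcome recording on the ward. That overlap is possible but not shown.

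A third objection is that stopping at 285 on an unadjusted superiority test at 0.05 has a price: the false-stop chance rises from 0.0385 to 0.0540, and 0.9 percentage points are lost from the chance of showing non-inferiority. This stands, and it is why the fix uses a strict level and limits the look to harm.

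**Conclusion.** The point holds as an inconsistency in oversight that should be corrected. C.1 and the stopping-rules section name incompatible committees. The text also does not fix whether the board meets, and may stop, at 285.

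The size is modest. At 20% v 14%, the expected gain from a stop at 285 is between 0.2 and 2.3 cases, depending on the level; at the strict level it is 0.2. The look matters mainly for a large, unexpected harm: 6.8 cases at the strict level if misoprostol did nothing. That is a worst case and not the protocol's expectation, since A.5.4 cites a 47% reduction with oral misoprostol against placebo. These figures rest on the assumed levels, equal arms and an immediate stop. The 6 and 12 months rest on even accrual. A board acting on judgement could also respond to deaths or other events that the calculation leaves out.

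It would be wrong to infer that the sample size or the final non-inferiority comparison is undermined; neither is affected. The absence of a numerical stopping boundary is not part of this point, because that may be set in another document.

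**What to change.** 1. In C.1, delete the sentence that makes the committee the senior ward staff, and direct the ad hoc safety referral to the board listed in the stopping-rules section.
2. In A.8 and C.1, name that board as the single committee for all four checks.
3. In the stopping-rules section, add 25% (285) as a safety review at which the board may stop for clear harm, using a strict level such as two-sided 0.001. Leave the reviews at 570, 855 and completion as they are.

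The listed board still includes a senior consultant of the trial hospital. A short statement that no member supervises the trial or its outcome recording would settle the remaining question of independence.

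The cost is a few edited sentences and one board meeting that is already promised twice. At the 0.001 level the false-stop chance rises by about 0.0004, and the chance of showing non-inferiority is essentially unchanged.

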#### **A.9 DISSEMINATION OF RESULTS**

Please outline what plans you have for dissemination of results.

*Guidance notes:*

*Where possible a mechanism should be in place to inform study participants of the outcomes of the study.*

*It is important that study findings are made known to local services / policy makers before they are discussed (e.g.) at international scientific meetings*

The study strategy for knowledge management and dissemination will be done by all investigators. Particularly, the dissemination of results for this study is motivated by both the academic and social impact, with a focus on the practical benefits for the key maternal health in Uganda and Low-resource settings.

The following points are highlights of the approach:

- Local meetings with key stakeholders in health policy, pharmaceutical sector, and other sectors of civil society and government
- Presentations at institutional, national and international conferences
- Specially tailored open-source materials (such as policy briefs, articles for magazines that reach policymakers or presentations to policymakers)

[figure not shown]

- Submission and publication of research findings to international high quality peer-reviewed journals

## SECTION B

### CONSEQUENCES FOR THE LOCAL COMMUNITY / ENVIRONMENT AND PARTICIPANTS

B.1 Outline the potential adverse effects, discomfort or risks that may result from the study in the following areas:

#### B.1.1 Participants

*Guidance note:*

*In addition to the physical effects of tissue sampling (for example blood sampling) it should be borne in mind that interviews and focus group discussions may sometimes trigger painful or distressing memories (e.g. questions about sexual practice or the death of a child)*

1. Most if not all questions that will be asked have been classified 'not sensitive or personal'. However, the participants may feel some anxiety answering some of them. In this case, they may choose not to answer some questions they feel uncomfortable
2. There is the risk of discomfort when blood is being drawn. There is also a small risk of bruising or infection. However, no more than 4mls of blood will be drawn for each of the two blood draws described. A participant may also refuse blood draws at any time.
3. There is a risk of bleeding following child birth for either of the study groups (oxytocin or misoprostol). In case this happens, routine procedures will be followed to give the participant additional therapeutic medications or procedures to treat or prevent further bleeding. Trained health professionals will also be available during and after delivery to treat this bleeding and answer any further questions

[figure not shown]

**B.1.2 Investigators**

*Guidance notes:*

*Include here (for example)*

- the biomedical risks to investigators (including local staff) involved in tissue sampling (e.g. Hepatitis B, HIV)
- the psychological consequences for social science investigators exposed to narratives of violence or severe grief
- the risks from the environment (e.g. in a war zone)

There are anticipated risks to Hepatitis B or HIV especially since the study is targeting measuring blood loss as its primary outcome.

**B.1.3 Members of the public**

We do not expect any adverse effects, discomfort or risks to members of the public.

**B.2 Outline what steps will be taken to minimise the adverse effects, discomfort or risks described above.**

**B.2.1 For participants**

*Guidance notes:*

*In biomedical research, appropriate use of anaesthesia prior to procedures (for example) is important.*

*For social science research it may be necessary to ensure that counselling services are available for those who re-live traumatic experiences through (for example) an in depth interview.*

- Most if not all questions that will be asked have been classified 'not sensitive or personal'. However, the participants may feel some anxiety answering some of them. In this case, they may choose not to answer some questions they feel uncomfortable
- The risk of discomfort, bruising or infection when blood is being drawn will be minimized by engaging highly trained personnel in phlebotomy. Also, no more than 4mls of blood will be drawn for each of the two blood draws described and a participant may also refuse blood draws at any time.
- There risk of bleeding following child birth for either of the study groups (oxytocin or misoprostol) will be managed by following routine procedures to give the participant additional therapeutic medications, bladder emptying, expulsion of clots or procedures to treat or prevent further bleeding. Trained health professionals will also be available during and after delivery to treat this bleeding and answer any further questions
- The research assistant will not discuss any information obtained from the participant with anyone other than the research and health care team

[figure not shown]

- Refusing to participate in this study at any time will not affect healthcare services that a participant would ideally obtain from the ward

